| **Data analysis** | Definition of the analysis groups   - Safety evaluation group: subject group in which safety follow-up was performed at least once after randomization and investigational product administration. - FAS evaluation group: subject group in which efficacy evaluation was performed at least once after randomization and investigational product administration. - Per Protocol(PP) evaluation group: subject group in which efficacy evaluation was performed at least once after randomization and investigational product administration, with no major protocol violation.   Statistical analysis   - FA group (Modified ITT) and PP group are both considered the main analysis groups according to ICH recommendations, as this is a non-inferiority study. - If missing data occur during the study, they are substituted using the multiple imputation method. - To prove non-inferiority of the experimental drug, the one-sided 97.5% confidence interval for the difference in change in LDQ at 12 weeks compared to baseline between the two groups is obtained. If the 97.5% upper confidence limit is less than the pre-specified non-inferiority margin of 0.40, the null hypothesis is rejected, and non-inferiority is proven. - All statistical analyses, except the non-inferiority analysis, are fundamentally based on the two-sided test with an alpha level of 0.05. - No interim analysis is to be performed. - The mean, standard deviation, median, minimum and maximum values for continuous variables, and frequency and proportion for categorical variables, must be presented on principle, and the incidence frequency is presented if necessary.   The change between each time of measurement, or from the baseline of demographical and other baseline data, safety data, and efficacy data, are summarized in descriptive statistical values by treatment group. Additionally, normal / abnormal changes in physical examination and laboratory test results are shown in partition tables by treatment group.  Co-administered drugs are recorded in ATC terminologies, and adverse events are standardized to system organ class (SOC) or preferred term (PT) using a medical dictionary (MedDRA or WHOART). |

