## Study withdrawal

A subject can withdraw from the study at any time and is not obliged to reveal the reason. A subject must be withdrawn from the study if one of the situations below arises:

- - Withdrawal of consent by the subject or the subject’s legal proxy.
  - The investigator’s assessment that continued participation in the study is harmful to the subject.
  - Adverse events too serious to continue the study (CTCAE grade 4 or 5) or difficulty with study participation as per the investigator’s assessment.
  - Serious protocol violation as per the sponsor or investigator’s assessment.
  - Unfit to continue in the study as per the sponsor or investigator’s assessment.
  - A subject’s wish to withdraw from the study for other reasons.

In cases of serious protocol violation as listed below, the corresponding subject must be excluded from the analysis (PP excepted):

- - Need for cessation of study participation due to the possibility of biasing the efficacy or safety evaluation of the experimental drug, or the violation of inclusion / exclusion criteria that can affect the safety of a subject, as per the investigator or sponsor’s assessment.
  - Notification by a subject of the use of another drug or treatment for the study’s target disease during the study period, and the investigator’s conclusion that the subject has no intention of ceasing the use of such drug or treatment.
  - The use or administration of drugs contraindicated for co-administration with the investigational product, as stated in Section [5.3.3](#_bookmark68).
  - Subjects who did not undergo washout for specified drugs before randomization.
  - Incorrect randomization.
  - Less than 80% compliance rate.

If the follow-up of a withdrawn subject is not possible, the investigator must make an effort to confirm the address and health status of subject. If a subject is withdrawn from the study, all efforts must be made to record, in full detail, the reason and situation leading to their withdrawal. If a subject withdraws early, the evaluation and treatment corresponding to Visit 3 must be conducted, when possible in addition to an appropriate assessment to determine the reason for early withdrawal, including any adverse reactions to the investigational products (refer to Section 6.1). The reason for withdrawal must be recorded in case report form for all cases.

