## Secondary evaluation

As secondary evaluation endpoints, the GSRS, pain VAS, and EQ-5D will be used.

- The GSRS (Gastrointestinal Symptom Rating Scale) consists of 15 short answer questions that can indicate a high correlation with gastroesophageal reflux disease, functional dyspepsia, and irritable bowel disease. (26, 27, 28)
- The VAS (visual analogue scale) will be used to evaluate the osteoarthritic pain experienced by the subjects. The VAS is a simple method that is widely used for pain evaluation in osteoarthritis patients. It has proven correlation with the survey-based Likert scale. (29)
- EQ-5D is a widely-used tool for the measurement of quality of life and health status. It includes the five categories of mobility, self-care, usual activities, pain / discomfort, and anxiety / depression. Each item is measured using the VAS, indicating subjective health status on a thermometer-shaped scale, as well as by multiple choice questions that evaluate health status as one of the following three stages: “no problem”, “some problems”, and “extreme problems”.

The study will also evaluate the incidence rate of gastrointestinal adverse events and the discontinuation rate due to gastrointestinal adverse events.

As an ancillary method to evaluate the pain control of the experimental drug and comparator, this study will also evaluate ancillary and rescue drug use after 8 weeks of oral administration of the study drugs, the average number of days of use, the average amount used per day (total amount used / days used) and the average amount of use during the study period (total amount used / study duration).

This study will also include compliance analysis. Compliance is defined as ‘(the actual number of administrations) / (the planned number of administrations)*100’, and patients with a compliance rate of 80% or above will be included in the PP (per-protocol) group analysis.

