## Definition of analysis sets

#### Target population

This study will be conducted on osteoarthritis patients of ≥50 years who can perform normal physical activity during the study period, with a pain VAS of 40 mm or more.

**Safety evaluation set: A population in which at least one safety follow-up observation is made after randomization and investigational product administration.**

**Full Analysis (FA) set: A population in which at least one efficacy evaluation is performed after randomization and investigational product administration.**

**Per-Protocol (PP) set: A population in which at least one efficacy evaluation is performed after randomization and investigational product administration, and in which there is no major protocol violation (violation of inclusion / exclusion criteria, violation of compliance). A compliance rate of 80% is used as the reference.**

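### Section 4.5.1 excludes serious protocol violators from every analysis except PP, the reverse of the analysis sets defined in the synopsis, 6.4.2 and 7.4

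*Protocol*

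**What the plan says.** Section 4.5.1 (Study withdrawal) first gives grounds for withdrawing a subject, including "Serious protocol violation as per the sponsor or investigator’s assessment". It then turns from withdrawal to analysis: "In cases of serious protocol violation as listed below, the corresponding subject must be excluded from the analysis (PP excepted"). Six violations follow. Two of them are "The use or administration of drugs contraindicated for co-administration with the investigational product, as stated in Section" 5.3.3, and "Less than 80% compliance rate".

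The analysis sets are defined elsewhere:

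- Synopsis, Data analysis: the PP group consists of subjects in whom "efficacy evaluation was performed at least once after randomization and investigational product administration, with no major protocol violation".
- Section 6.4.2: "patients with a compliance rate of 80% or above will be included in the PP (per-protocol) group analysis".
- Section 7.4: "Full Analysis (FA) set: A population in which at least one efficacy evaluation is performed after randomization and investigational product administration". The PP definition there adds the absence of a major violation, with 80% compliance as the reference. The safety set needs only randomization, dosing and one safety follow-up.
- Role of the sets, synopsis: "FA group (Modified ITT) and PP group are both considered the main analysis groups". Section 7.5.1 repeats that the primary endpoint is analysed in both.

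**The concern.** The bracket in 4.5.1 names PP as the one analysis to which the exclusion does not apply. PP is the set that exists to leave violators out, and FA is the set that exists to keep them in. The sentence is worded as an obligation, so someone building the data sets from 4.5.1 would build both main sets the wrong way round. The word analysis carries no qualifier, so the safety set is reached as well. Subjects who took a prohibited NSAID, or who broke an eligibility criterion that matters for safety, would then drop out of the safety analysis of an NSAID trial.

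In a non-inferiority trial the agreement of FA and PP is part of the evidence. FA shows the result in nearly everyone treated; PP shows it in those who took the treatment as planned. If FA loses its violators, it no longer does the job that the synopsis gives it by calling it a modified ITT group.

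**Working it through.** **Set membership.** Take a subject who was randomized and dosed, had safety follow-up and a post-dose LDQ, and whose compliance was below 80%.

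| Rule followed | FA | PP | Safety |
|---|---|---|---|
| 4.5.1, literally | out | not excluded | out |
| Synopsis, 6.4.2 and 7.4 | in | out | in |
| 4.5.1 read as PP-only exclusion | in | out | in |

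The first two rows disagree in every column. The third row agrees with the second, which is why PP-only exclusion is the likely intent. Section 5.3.3 points the same way: its own sanction for certain unassessed drugs is exclusion from PP.

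**Does withdrawal make the question moot?** No.

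- Section 4.5.1 asks for the Visit 3 evaluations at early withdrawal when possible, and the early termination visit in 6.1 includes the LDQ. A withdrawn violator can therefore still meet the FA definition.
- Section 7.5.3 derives compliance from returned product, which is collected at Visit 3 or at early termination. No visit is scheduled between Day 1 and the end-of-study visit at about Day 84. Low compliance will usually come to light only when follow-up is over.

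**The plan's own figure.** Inputs from 7.1: SD 0.65, margin 0.40, one-sided alpha 0.025, power 80%, drop-out 20%.

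- n per arm = 2 × 0.65² × (1.96 + 0.842)² / 0.40² = 41.46, rounded up to 42.
- Enrolled per arm = 42 / 0.80 = 52.5, rounded up to 53, so 106 in total.

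Both figures reproduce, and the point disputes neither.

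**Why no bound on the effect is given.** Use SE = 0.65 × √(2/n) and power at zero true difference = Φ(0.40/SE − 1.96).

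| n per arm | SE | Power |
|---|---|---|
| 53 | 0.1263 | 88.6% |
| 42 | 0.1418 | 80.5% |
| 31 | 0.165 | about 68% |

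It would be easy to start FA at 53, remove at most 53 − 42 = 11 violators per arm, and call 80.5% the floor. That fails. Drop-outs without a post-dose LDQ are already outside FA, and violators can come on top of them. Starting at 42 and removing 11 gives 31 and about 68%. Removing an assumed 5% to 20% of 42 gives 78.5% to 71.3%. These are illustrations only, because the protocol states no violator rate.

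**Per-subject scale.** Adding or removing one subject who lies one SD from the rest of the arm moves that arm's mean by 0.65/53 = 0.012, or 0.65/42 = 0.015. That is 3% to 4% of the margin. The sign depends on the subject and the arm and cannot be known in advance.

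**The case against.** The strongest reply is that this is a slip, probably of translation. Section 7.4 is where the sets are defined, 4.5.1 is about withdrawal, and every other place in the protocol agrees with PP-only exclusion, so a competent analyst would follow 7.4. As to intent, that stands, and the point should not be presented as a faulty design choice. But the sentence is an explicit instruction on who enters the primary analysis. An SAP could choose the right rule, but it would then depart from 4.5.1 as written.

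Three stronger readings are tempting and are not supported.

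- **Violators end up in neither main set.** This happens only if 4.5.1 is used for FA and 7.4 for PP. It is neither the effect of 4.5.1 taken alone nor the likely intent, and the point does not need it.
- **Sections 4.5.1 and 5.3.3 contradict each other on listed drugs prescribed by the investigator.** Section 5.3.3 lets the investigator give any drug deemed necessary and states a PP exclusion for an influential drug given without assessment. It does not say that this is the only ground. Section 4.5.1 lists 5.3.3 drugs without exception. Exclusion criterion 20 also refers to 5.3.3, and the 7.4 bracket counts a breach of the exclusion criteria as a major violation. The sections can be read together: permission to treat is not a promise of PP membership. Clearer text would help, but there is no established conflict.
- **The loss of power is limited to a known amount.** The arithmetic above shows that the obvious floor is not one.

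**Conclusion.** The point holds as an internal contradiction about set membership. As written, 4.5.1 spares violators from exclusion in PP and removes them from FA and safety, against the synopsis, 6.4.2 and 7.4. It deserves correction because FA and PP jointly carry the non-inferiority conclusion. The harm is to the meaning of the two sets. Its size in LDQ units or power is unknown, since it depends on how many violators occur, in which arm, and how their LDQ changes differ from the rest.

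The conclusion rests on the literal sense of the bracket and on no numerical assumption. If the sponsor confirms that PP-only exclusion was always meant, the planned analysis is sound and only the sentence needs changing.

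**What to change.** In 4.5.1, replace the phrase about exclusion from the analysis with: *excluded from the PP analysis only; the subject remains in the FA and safety sets if the definitions in 7.4 are met*. The condition matters. Without it, an undosed subject, or one with no post-dose efficacy evaluation, would be put into FA contrary to 7.4.

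Optional clarifications in the same amendment:

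- State in 5.3.3 and 7.4 that use of a listed 5.3.3 drug is a major violation for PP, as 4.5.1 already says. The investigator's freedom to treat is unchanged.
- Align the low-dose aspirin limit, which is ≤325 mg/day in 5.3.2 and <325 mg/day in 5.3.3, at ≤325 mg/day. Only a dose of exactly 325 mg is affected.

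The cost is a wording amendment, best made before the code is opened. Co-administered drugs and returned product are already recorded, so no new data or visits are needed, and the sample size stays at 106. PP exclusion takes subjects out after randomization, which can favour non-inferiority. The planned reading of PP beside a complete FA set is the safeguard, and the correction preserves it.

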## Discontinuation of investigational product use

Administration of the investigational product must be discontinued if any of the below situations arise during the study:

- - Fulfillment of exclusion criteria that can affect the safety of a subject and necessitate discontinuation of the investigational product administration, as per the clinical assessment by the investigator or sponsor.
  - Adverse events for which temporary or permanent discontinuation of the investigational products is necessary, as per the assessment of the investigator or subject.
  - Administration of drugs contraindicated for co-administration that require discontinuation of the investigational products, as stated in Section 5.3.3.
  - Serious non-compliance to administration of the investigational product.

The investigator must ensure that the administration of the investigational products is as planned. If investigational product use is discontinued by a subject, all observations necessary and possible must be made and recorded, as in the case of study withdrawal. In all cases of discontinuation of the investigational product, the reason, situation, and duration must be recorded in case report form.

## Substitution of subject

This study does not allow for the substitution of a withdrawn subject.

## Addition of new dosage groups

This study does not allow for additional dosage groups.

## Early termination of study

The study can be terminated early in the following cases (in which there is new information regarding negative effects of the investigational products on the risk / benefit ratio for the subjects):

- - Evidence of lack of efficacy.
  - New and important drug-related adverse events or an unexpectedly high incidence rate or severity of one or more previously known adverse events.
  - Other safety-related reasons.
  - An inability to medically or ethically justify continuation of the study, as per the sponsor’s assessment.
  - The rate of subject enrolment at a study site is deemed to hinder the enrolment of the required number of subjects for the study.
  - The cessation of sale or supply of the investigational products.

If this study is terminated early, a government regulatory authority or clinical study review committee will be notified according to the relevant regulations. The study can be suspended or terminated by a request from the government regulatory authority.

## Termination of study

In this study, Visit 3 is defined as the “end of study (trial) visit’, and subjects who have completed Visit 3 are defined as completed subjects. If the following situations occur, this study will not be deemed completed:

- - There are remaining subjects who are still due to receive investigational products.
  - The pre-specified visit schedule at a study site has not been completed.

If a subject misses a visit or is lost to follow-up despite reasonable requests for a visit, the corresponding subject will be deemed to have terminated the study participation. No further evaluation will be conducted after study termination.

## Other considerations

Subjects must limit any external factors that may affect laboratory test results or induce interactions with the investigational products (alcohol, excessive exercise, etc.).

#### Diet

Subjects must be fasted from 10 pm the night before the laboratory test is due to be conducted.

#### Alcohol

Subjects should abstain from a weekly alcohol intake of 21 standard drinks (3 drinks / day) during the study period and from any alcohol intake for 72 hours prior to the laboratory tests.

#### Exercise

Excessive exercise should be avoided the day before the laboratory tests, including the screening tests.

# Investigational product and other study drugs

“Investigational medicinal product” includes the experimental drug and the control drug.

## Investigational product

## Experimental drug

## Product name / code

Naxozol tablet.

## Pharmaceutical form

Rectangular, pale yellow, film-coated tablet.

## Qualitative and quantitative composition

Naproxen (USP) 500 mg, and esomeprazole strontium tetrahydrate 24.60 mg (as esomeprazole 20 mg), per tablet.

## Storage conditions

Sealed container, room temperature (1 - 30℃); shelf life: 24 months from manufacture date.

## Experimental drug placebo

Rectangular, pale yellow, film-coated tablet that does not contain the active ingredients but has the same pharmaceutical form as the experimental drug.

## Control drug

## Product name/code

Celebrex capsule.

## Pharmaceutical form

White capsule with two yellow bands containing white to pale yellow powder.

## Qualitative and quantitative composition

Celecoxib 200 mg per capsule.

## Storage conditions

Sealed container, room temperature (15 - 30℃).

## 5.1.4. Control drug placebo

White capsule with two yellow bands that does not contain the active ingredient but does contain white to pale yellow powder and has the same pharmaceutical form as the experimental drug.

## Expected dosage and administration

## Expected dosage and administration of the experimental drug

* Adult: 1 tablet twice daily (naproxen 500 mg / esomeprazole 20 mg) orally. During this study, 1 tablet of the experimental drug and 1 control drug placebo capsule will be administered concomitantly 30-60 minutes before a meal. This drug should not be split, chewed, or crushed, and should be taken whole with water. Administration 30-60 minutes before food is recommended.

- - Effect on laboratory values:

1. This drug may interfere with platelet aggregation and increase bleeding time. Caution must be taken when measuring bleeding time.
2. This drug may affect the measurement of 17-ketogenic steroids and should be temporarily discontinued 72 hours before measurement.
3. Naproxen may affect urinalysis of 5-hydroxyindoleacetic acid (5-HIAA).

## Expected dosage and administration of the control drug

* During this study, 1 capsule of the control drug and 1 experimental drug placebo tablet should be administered 30-60 minutes before a meal. The minimum recommended dose should be adjusted for each patient. This drug can be administered irrespective of food times.

1. Osteoarthritis (degenerative arthritis): 200 mg celecoxib, once daily.
2. Rheumatoid arthritis: 200 mg celecoxib, once daily.
3. Ankylosing spondylitis: 200 mg celecoxib, once daily. If no effect is seen within 6 weeks, the dose may be increased to 400 mg/day. If no effect is seen at 400 mg / day within 6 weeks, another treatment should be considered.
4. Acute pain and primary menstrual pain: the initial recommended dose is 400 mg celecoxib. An additional 200 mg may be given on the first day, if needed. From the second day of administration, 200 mg per administration, once a day, is given as a recommended dose when needed.
5. Hepatic impairment: the dose should be reduced to approximately 50% of the daily recommended dose in patients with moderate hepatic impairment (Child-Pugh class II).
   - Effect on laboratory values:
6. Patients on long-term NSAID therapy must undergo a regular complete blood count, physical examination, and blood chemistry test. If abnormal liver function or renal function persists or worsens, this drug must be discontinued.
7. As with other NSAIDs, in clinical studies BUN levels were elevated more frequently in patients on celecoxib than in those given placebo, though without confirmed clinical significance.

## Other drugs used in the study

## Concomitant pharmacological therapy and treatment

## Supplementary medication

If dyspepsia due to the investigational product is severe, the following supplementary medication is allowed for the subject:

- - - - - Almagate (Hanmi Almagate 500 mg tablet); a maximum of 6 tablets / day and 30 - 50 tablets in total per person.

For the above medication, the dose and duration of administration must be recorded on the case report form.

- - - - - Criteria for administration of the supplementary medication:

For the entire duration of the study, if the symptoms of dyspepsia become unacceptable, a maximum of 6 Almagate (Hanmi Almagate 500 mg) tablets over 24 hours per subject will be allowed for additional gastrointestinal protective therapy. For this, an adequate amount of supplementary medication should be distributed to the randomized subjects. Subjects should be educated not to exceed 6 Almagate (Hanmi Almagate 500 mg tablet) tablets over 24 hours. The amount of supplementary medication used must be recorded in the subject file, and the remaining amount should be returned for confirmation of the amount used. The above criteria must be conveyed to the subjects by the investigator.

